#### 2.7.3. C-Epworth Sleepiness Scale (ESS)

The ESS is used to assess the level of daytime sleepiness [28]. The ESS is a self-administered eight-item questionnaire that asks about the chance of falling asleep during performing eight daily activities on a scale from 0 to 3. The total score ranges from 0 to 24, with a higher score indicating worse daytime sleepiness.

### 2.8. Secondary Outcome Measures

#### 2.8.1. A-PSQI

PSQI is a self-reported questionnaire with 19 questions that measure various aspects of sleep quality [29]. The response to the questionnaire is rated on a scale from 0 to 3, with 0 indicating no sleep difficulty and 3 indicating severe sleep difficulties. The PSQI global score ranges from 0 to 21, with a higher score indicating poor sleep quality. Individuals with a PSQI global score of >5 can be classified as having poor sleep quality. The PSQI has good psychometric properties in sport populations [30].

#### 2.8.2. B-Depression Anxiety Stress Scale-21 (DASS-21)

The DASS is composed of 21 items that assess the psychological symptoms of depression, anxiety, and stress [31]. The response to DASS items involves using a Likert scale that ranges between 0 and 3, with a higher score indicating a worse psychological status. It has been recommended to use the DASS-21 with athletes over other measures of mental health [32].

#### 2.8.3. C-Medical Outcome Study Short-Form Survey 12-Item (SF-12)

The SF-12 is a self-reported questionnaire that assesses the impact of health on an individual’s quality of life [33]. The SF-12 consists of 8 domains: physical function, role (physical), bodily pain, general health, vitality, social functioning, role (emotional), and mental health. The possible total scores range between 0 and 100, with higher scores demonstrating better quality of life [33].

### 2.9. Intervention

Depending on the randomization allocation, participants will receive either a real tDCS or sham tDCS protocol for three sessions per week for 2 weeks, with a total of six sessions. 

### 2.10. Treatment Group (Real tDCS Group)

Direct current will be delivered from a battery-driven constant current stimulator (Neuro-electric, NIC, Barcelona, Spain). Each participant will receive 20 min of bilateral anodal tDCS (positively charged electrode). Anodal electrodes are placed over the right and left DLPFC (F3 and F4) according to the 10–10 international EEG system [34] (Figure 2) with small-size (1 cm^2^) sponge electrodes soaked in saline with an intensity of 1.5 mA (0.057 mA/cm^2^ in density). This will be repeated six times during the 2 weeks. The bilateral cathodes (negatively charged electrodes) will be placed over the left and right supraorbital areas as reference codes (FP1 and FP2).

All participants will be asked to remain minimally active during this time and engage in either light watching of television or listening to the radio.

### 2.11. Control Group (Sham tDCS Group)

For sham stimulation, the electrodes will be placed in the same positions as for the real tDCS stimulation. However, a constant current of 1.5 mA will only be delivered for 30 s (30-s ramp on). This stimulation protocol will provide an initial period of a tingling sensation similar to that one would perceive during the real tDCS protocol. The data and instructions on the device display will not differ from the real tDCS settings.

### 2.12. Statistical Analysis

The participants’ characteristics and outcome measures at baseline will be compared between the two groups using the Kruskal–Wallis test. Data will be screened for missing data, normality, and outliers. For variables that are not normally distributed, non-parametric tests will be used. The normally distributed data will be analyzed by repeated measures analysis of variance (ANOVA) to evaluate the therapeutic effect and changes between the two groups and within groups (group: sham vs. real tDCS) × (time: pre- vs. post-intervention vs. 1-month follow-up). Post hoc analysis will be applied to determine the exact groups with significant changes if significant findings appear. For the variables not normally distributed, we will use Friedmann’s test. The correlation between the changes in the Actigraph results with the athletes’ characteristics, DAAS-21, SF-12 pain, general health, role (emotional), and mental health domains at baseline will be analyzed by repeated measures linear regressions to understand the mechanism of improvement. The data will be analyzed using SPSS software, and a conservative *p*-value of 0.05 will be considered.

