### 2.3. Randomization Allocation and Blinding

Participants will be allocated consecutively to randomization using the tool from the randomization.com website (http://www.randomization.com, Accessed date: 10 May 2022) by a researcher who is not in contact with any participant. The investigators will use the suggested first generation for RCT studies. The included participants will be randomly allocated to the parallel tDCS or control groups in a balanced allocation ratio of 1:1. Allocation concealment will continue until the end of the study.

All assessment, evaluation, and intervention procedures will be carried out by examiners who will be blinded to the allocation of the participants. A trained research assistant that is not otherwise connected with the study will set the stimulation characteristics as indicated by the information in a sealed envelope opened upon the participants’ visits (real or sham). The mode of stimulation will not be revealed to the participants or investigators.

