### 2.6. Assessments and Outcome Measures

Demographics include the date of birth, educational level, marital status, weight, and height. Health-related questions concern the diagnosis of any other disorders and current medications used. Sport-related information that will be gathered includes the type and level of sport, number of years in practice, number of times they practice per week, and for how long.

All assessment instruments will be used in their validated Arabic versions. The primary and secondary outcome measures include both subjective and objective sleep outcomes.

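### Section 2.12 names the Kruskal–Wallis test for every baseline characteristic, but for unordered multi-category variables such as type of sport its p-value depends on arbitrary category codes (minor)

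*Protocol article*

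**What the plan says.** Section 2.12 opens with the rule that participant characteristics and outcome measures at baseline "will be compared between the two groups using the Kruskal–Wallis test". It names one test and makes no distinction by type of variable.

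Section 2.6 shows what the characteristics are. On demographics: "Demographics include the date of birth, educational level, marital status, weight, and height". On health: "Health-related questions concern the diagnosis of any other disorders and current medications used". The sport-related items are "type and level of sport, number of years in practice, number of times they practice per week, and for how long".

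Allocation is random; under section 2.3 participants will be "randomly allocated to the parallel tDCS or control groups in a balanced allocation ratio of 1:1". The only significance level given in section 2.12 is the general one: "a conservative *p*-value of 0.05 will be considered". The section does not mention a chi-square or Fisher test. Its fallback for variables that are not normally distributed is a non-parametric test, which does not deal with unordered categories. It does not say what would follow from a significant baseline difference.

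**The concern.** Kruskal–Wallis compares ranks. Ranks mean something for weight, for years of practice, or for an ordered scale such as educational level. Type of sport has no order, and section 2.1 recruits from clubs and teams in different sports, so it will have several categories. Marital status has no order either if more than two levels are recorded. For such a variable the ranks come from whatever numbers the data file assigns to the categories. Two analysts with the same data and different code lists could report opposite results, and neither p-value would answer whether the mix of sports differs between arms.

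The second problem is the testing itself. Under random allocation any baseline difference arises by chance, so a significance test addresses a hypothesis already known to be true. Across two dozen or so variables, some p-values below 0.05 are to be expected. A reader may take one as a sign of faulty randomisation. A non-significant result with 42 per arm is weak evidence of balance on a prognostic score.

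At stake is the readability of the baseline table, not the estimate of the treatment effect.

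**Working it through.** The plan states no figure for the baseline comparison. The inputs are the total of 84 (section 2.4) and the 1:1 ratio (section 2.3), hence 84 / 2 = 42 per arm, and the level of 0.05 (section 2.12). The category counts below are made up for illustration, because the documents give none. The dependence on coding is a property of the test and does not rest on these counts.

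**1. Five unordered categories.** Counts 12/6/9/5/10 against 5/12/7/11/7, each summing to 42.
- Pearson chi-square on 4 degrees of freedom is 7.91, p = 0.095, whatever the numbering.
- Kruskal–Wallis over all 5! = 120 numberings: p from 0.0071 to 0.993. In 26 of 120 numberings (21.7%), p is below 0.05.

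**2. Three unordered categories.**

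| Counts by arm | Chi-square p | Kruskal–Wallis p, by coding |
|---|---|---|
| 24/10/8 vs 14/20/8 | 0.051 | 0.100 or 0.016 |
| 10/22/10 vs 20/2/20 | 0.000009 | 1.00 or 0.00007 |

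In the second row a gross difference between arms is either found or missed entirely, depending on which category is numbered in the middle.

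**3. Where the test is acceptable.** With two groups, Kruskal–Wallis is the Mann–Whitney test, which suits continuous and ordinal variables. For a binary variable its statistic is chi-square × (N − 1)/N. With counts 25/17 vs 15/27 this is 4.773 × 83/84 = 4.716, so p = 0.0299 against 0.0289. The difference is immaterial.

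**4. Type I error on nominal data.** With a three-level variable simulated under the null, Kruskal–Wallis rejected in 5.3% of runs. Re-randomising the pooled five-sport counts (17/18/16/16/17) gave 5.6% in 8,000 runs. The error rate therefore stays close to 5% for a coding fixed in advance.

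**5. Number of baseline tests.** Section 2.6 gives 5 demographic + 2 health + 5 sport items = 12. Sections 2.7 and 2.8 add the outcomes:
- With totals: 4 actigraphy parameters + ISI + ESS + PSQI + DASS-21 + SF-12 = 9, so 12 + 9 = 21 variables.
- With subscales: 4 + 1 + 1 + 1 + 3 DASS-21 scales + 8 SF-12 domains = 18, so 12 + 18 = 30 variables.

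**6. Chance findings at 0.05.** The expected number is 0.05 × 21 = 1.05 to 0.05 × 30 = 1.5. If the tests were independent, the chance of at least one is 1 − 0.95^21 = 0.66 to 1 − 0.95^30 = 0.79. The documents give no correlations, so these are assumed:

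| Assumption | 21 variables | 30 variables |
|---|---|---|
| Independent | 66% | 79% |
| Outcome scores correlated 0.3 to 0.7, characteristics independent | 63% to 57% | 73% to 61% |
| All variables correlated 0.5 | 43% | 51% |

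**7. T0 as a covariate.** Assume equal variances at T0 and follow-up and a correlation ρ between them. The variance of the covariate-adjusted arm difference, relative to that of the change-score difference, is (1 − ρ²) / [2(1 − ρ)] = (1 + ρ)/2. At ρ = 0.3 this is 0.65, and at ρ = 0.7 it is 0.85.

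**The case against.** The case on the other side is strong on scope. A rank test on a coding fixed in advance keeps its error rate under randomisation (step 4), so a reader who infers inflated false positives goes too far. Few variables are affected: type of sport and, with more than two levels, marital status. Diagnoses and medications recorded as yes or no behave almost as under chi-square (step 3). No decision hangs on these tests: section 2.12 does not use them to choose covariates, adjust results or judge the randomisation, so any later misuse is conjecture about readers. The 79% takes the largest count of variables and assumes independence, which is implausible when sleep efficiency is a ratio of two other listed parameters and ISI and PSQI both measure sleep impairment. It is also tempting to say that the plan ignores baseline values, but T0 is a level of time in the repeated-measures ANOVA, so the group-by-time term already compares change from T0. Finally, an article condenses, and a test for each type of variable is commonly left to a fuller document.

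All of this stands except the last argument, which stands only in part. The article is not silent on the choice of test: it names one, without exception, and that test does not suit some of the variables it is assigned to. An analysis plan that followed the sentence would inherit the fault, and one that did not would depart from the published text.

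**Conclusion.** The point holds as a minor one. As written, section 2.12 yields a p-value for type of sport, and for marital status if it has more than two levels, that depends on how categories are numbered. In the illustration it ranges from 0.007 to 0.993 on identical data. For the other baseline variables the choice of test is acceptable.

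At least one chance imbalance is likely but not certain: 66% to 79% under independence, 57% to 73% if only the outcome scores are correlated, and about 43% to 51% if everything is correlated at 0.5. The correlations are assumptions.

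The documents do not support a reading in which the efficacy result or the randomisation is compromised, because the baseline tests do not enter the efficacy analysis.

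**What to change.** Replace the opening sentence of section 2.12 with a statement that baseline characteristics and outcomes will be summarised by arm, without significance tests: mean (SD) or median (IQR) for continuous and score variables, counts and percentages for categorical ones. If tests are kept, use chi-square or Fisher's exact test for nominal variables and state that no decision rests on them.

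As a separate gain in precision, use each outcome's T0 value as a covariate in the between-arm model of T1 and T2, rather than only as a level of time. Under the assumptions in step 7, the variance falls to 0.65 to 0.85 of the change-score variance.

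The baseline change costs one sentence, and the covariate needs one more in the model description. Neither needs new data or participants, since T0 is already collected. The only downside is a baseline table without a p-value column.

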## 2. Materials and Methods

### 2.1. Participants

Participant recruitment began in May 2022 and will continue until December 2023. Athletes from the national clubs and teams of different sports in Jordan will be invited to participate in this study. Elite athletes are eligible if they satisfy the following criteria: (1) being 16 years of age and older and (2) have a complaint of sleep impairment determined by a global score >5 on the Pittsburgh Sleep Quality Index (PSQI).

Exclusion criteria for the study will include any of the following: the use of sleep medications or other interventions interfering with sleep and sleepiness, more than one concussion in the past year, using a pacemaker, pregnancy, diagnosis of migraines with a high frequency of episodes, wearing a metal implant, or epilepsy. 

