### 2.4. Sample Size Calculation

The sample size was calculated using G*Power software according to the study of Charest et al. (2021) [23]. The study found d = 0.7012 for the Cohen’s effect size of tDCS on PSQI as the screening outcome of this study. Based on a 0.7012 effect size, bidirectional alpha of 0.05, and 80% test power, a minimum of 70 participants are required for this study. The sample will be increased by 20% to compensate for possible dropouts, and an overall sample of 84 participants will be included in this study.

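### Observed normality chooses each outcome's test, and the named fallback, Friedman's test, has no group factor, so a re-routed outcome loses its real-versus-sham comparison

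*Protocol article*

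**What the plan says.** Section 2.12 of the protocol article sets up a screen and two branches.

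- Screen: "Data will be screened for missing data, normality, and outliers".
- Normal branch: "The normally distributed data will be analyzed by repeated measures analysis of variance (ANOVA"), with group (sham, real) and time (pre, post, 1-month follow-up) as factors.
- Other branch, general rule: "For variables that are not normally distributed, non-parametric tests will be used".
- Other branch, named test: "For the variables not normally distributed, we will use Friedmann’s test".

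Kruskal–Wallis, which does compare groups, appears in the same section only for the baseline comparison.

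Section 2.1 admits athletes with sleep impairment "determined by a global score >5 on the Pittsburgh Sleep Quality Index (PSQI"). Section 2.8.1 lists PSQI as a secondary outcome and gives its scale: "The PSQI global score ranges from 0 to 21". Section 2.4 bases the sample size on PSQI. Section 2.7 lists the primary outcomes: four actigraphy parameters, ISI and ESS.

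**The concern.** Three features of the rule combine badly.

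1. The test for each outcome, including the six primary ones, is settled after the data are seen. Related sleep measures may end up under different tests.
2. The rule speaks of variables, whereas a repeated measures ANOVA needs roughly normal residuals. The entry cut-off makes baseline PSQI lopsided by design without harming a comparison between randomised arms.
3. Friedman's test ranks each participant's own visits and asks whether the visits differ. It has no term for treatment. An outcome sent there has no test of real against sham stimulation, which is the question of the trial.

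What remains is a pooled time effect or two separate within-arm results. Either can be significant because participants were selected for poor sleep and drift back towards their average, or because both arms improve.

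**Working it through.** **The plan's own figure.** Inputs from section 2.4: d = 0.7012, two-sided alpha 0.05, power 80%, N = 70, raised by 20%.

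- Two-sample t-test (noncentral t): 32.9, so 33 per arm, total 66, power 0.801. This does not give 70.
- Mann–Whitney by asymptotic relative efficiency with a normal parent: 32.9 / (3/π) ≈ 34.5, so 35 per arm, total 70, power 0.806. This gives 70 exactly.
- 70 × 1.2 = 84, as stated.

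The article does not say which test was selected, so the Mann–Whitney match is inferred from the number. At 35 per arm the t-test has power 0.824.

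**How often would the screen fire?** The article gives no means, SDs, within-person correlation, normality test or threshold. Assumed here: integer scores, baseline PSQI restricted to 6-21, Shapiro-Wilk at 0.05.

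| Variable screened | Assumption | Rejected |
|---|---|---|
| Baseline PSQI, n = 84 | latent mean 6, 7, 8 or 9, SD 3 | 99.9-100% |
| Baseline PSQI, n = 84 | latent mean 10, SD 3 | 92% |
| Baseline PSQI, n = 84 | latent mean 11, SD 2.5 | 52% |
| Baseline PSQI, one arm (n = 42) | across the settings tried | 22-100% |
| T1 PSQI, 35 per arm | latent mean 7 or 9, SD 3 | 16-42% |
| Baseline-adjusted residuals, 35 per arm | latent mean 7 or 9, SD 3 | 4-7% |
| Wake after sleep onset, n = 84 | lognormal, sigma 0.3 / 0.5 / 0.7 | 79% / 99.6% / 100% |
| ESS, n = 84 | mean 8 / mean 6, SD 4, floored at 0 | 16% / 77% |
| ISI, n = 84 | mean 11, SD 4 | 11% |

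Part of the PSQI rejection comes from whole-number scoring. At mean 11, SD 2.5, n = 42, it is 14% without the cut-off and 22% with it.

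**Does the screen protect anything?** With truncated PSQI, 35 per arm and correlation 0.5, the ungated group × time ANOVA had type I error 4.4-5.2%. A two-sample t-test gave 5.2% for truncated PSQI and 4.9% for a lognormal with sigma 0.7. The ANOVA itself was not checked for a skewed wake after sleep onset.

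**Is the fallback merely less efficient?** Take a true shift of 0.7012 × 3 ≈ 2.1 points at 35 per arm:

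- group × time ANOVA: 0.88-0.90
- baseline-adjusted comparison at T1: 0.90-0.91
- t-test on change: 0.85-0.87
- Mann–Whitney on change: 0.82-0.85

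A between-group rank test on change thus costs about 1-3 points against the t-test on change, and 5-9 points against the baseline-adjusted model.

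**What does Friedman's test return?** Latent mean 7 or 9, SD 3, correlation 0.5, 35 per arm:

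| Treatment effect | Change common to both arms | Pooled Friedman significant | Real arm significant, sham not |
|---|---|---|---|
| none | none | 52% / 13% | 20% / 8% |
| none | 1.5 points | 100% / 99.9% | 1% / 6% |
| 2.1 points | none | 100% / 95% | 71% / 92% |
| 2.1 points | 1.5 points | 100% / 100% | 0.5% / 7% |

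(Figures are for mean 7 / mean 9.) The pooled result does not distinguish a treatment effect from none. Comparing the two within-arm results gives false positives in the first row and misses nearly every true effect in the last.

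**The case against.** **The article is condensed, and an SAP may settle the details.** This stands for the choice of normality test, its threshold, the visit screened, and whether values or residuals are examined. It does not reach the rule itself: the article states that normality picks the branch and names Friedman's test as the alternative. An SAP that filled in those details would still be carrying out that rule. The plural in the general rule could leave room for a between-group rank test, but none is named for the treatment effect.

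**A reader might infer that PSQI is bound to fail the screen.** The documents do not support certainty. The cut-off acts on T0 only, T1 and T2 are not truncated, PSQI is a secondary outcome, and every distribution used above is assumed. The entry rule truncates none of the primary outcomes, so exposure there rests on assumed shapes and varies widely.

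**A reader might infer that the non-parametric branch is simply weaker.** A between-group rank test would lose little, and the stated N even matches one. The defect is the missing group factor.

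**A reader might put a figure on how often a perfectly normal outcome is re-routed.** That needs a rule that any single failed visit or arm re-routes it, and independent screens. The article states neither, and repeated visits are correlated.

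**A reader might say the rule removes promised effect estimates and intervals.** Section 2.12 promises none in either branch.

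**Conclusion.** The concern holds in this form. Section 2.12 lets the observed data choose between a test that compares the arms over time and one that cannot compare them. Baseline PSQI would probably be re-routed if raw baseline scores decide the branch, and so would wake after sleep onset if it is right-skewed. For truncated PSQI the screen brings no material gain in error control.

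The size depends on assumptions. Over latent PSQI means of 6-11 and SDs of 2.5-3, pooled Friedman's test was significant with no treatment effect and no common change in 5-91% of trials, and in about 100% when both arms improved by 1.5 points. The absence of a group factor needs no assumption: it is a property of the named test. This should be changed before unblinding.

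**What to change.** Delete the normality screen as a way of choosing the test, and delete Friedman's test as an analysis of the treatment effect. For every outcome (time in bed, actual sleep time, wake after sleep onset, sleep efficiency, ISI, ESS, PSQI, DASS-21 and SF-12), name one between-arm comparison at T1 and T2 adjusted for the T0 value. Use the log scale for wake after sleep onset and the natural scale for the others. Check model residuals, not raw variables. Keep a between-group rank analysis or a bootstrap interval as a sensitivity analysis only.

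The cost is wording, provided it is done before unblinding. The one statistical price is that a mean difference may be slightly less efficient than a rank test for a very skewed outcome. The log scale and the sensitivity analysis cover most of that.

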### 2.5. Procedures

The research procedure will be explained to eligible athletes if they agree to participate. Informed consent will be obtained from each participant. Figure 1 demonstrates the CONSORT flow diagram for this study. Baseline assessments (T0) will be conducted for demographic, health, and sport-related information, clinical characteristics, and primary and secondary outcome measures at baseline. Post intervention assessments (T1) for comparing the immediate efficacy between the two groups of primary and secondary outcome measures will be performed directly after completion of the intervention protocol. Follow-up assessments (T2) will be conducted 1 month after the end of the intervention.

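### For normally distributed outcomes, a repeated-measures ANOVA with baseline as a level of time is valid but usually less powerful than a baseline-adjusted contrast at one pre-named visit

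*Protocol article*

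**What the plan says.** Section 2.12 (Statistical Analysis) assigns normally distributed outcomes to one method: "The normally distributed data will be analyzed by repeated measures analysis of variance (ANOVA) to evaluate the therapeutic effect". The factors are given as "group: sham vs. real tDCS) × (time: pre- vs. post-intervention vs. 1-month follow-up". Visit-level or group-level comparisons are conditional: "Post hoc analysis will be applied to determine the exact groups with significant changes if significant findings appear". On incomplete data the section says only "Data will be screened for missing data, normality, and outliers", and on software "The data will be analyzed using SPSS software". It names no baseline covariate and no treatment contrast at a single visit. Variables that are not normally distributed go to a Friedman test and lie outside this point.

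Section 2.5 (Procedures) has the outcomes measured at all three visits. For T0 it says: "Baseline assessments (T0) will be conducted for demographic, health, and sport-related information, clinical characteristics, and primary and secondary outcome measures at baseline". It describes T1, directly after the intervention, as the comparison of immediate efficacy, and puts T2 one month after the end of the intervention.

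Section 2.4 (Sample Size Calculation) uses d = 0.7012, two-sided alpha 0.05 and 80% power to reach 70 participants. It then says: "The sample will be increased by 20% to compensate for possible dropouts", giving 84.

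**The concern.** Three features of the chosen analysis cost information.

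- **Baseline is a response.** Randomisation makes the expected arm difference at T0 zero. Used as a covariate, the T0 value would remove outcome variance. Used as a level of time, it enters as one more noisy response.
- **The test is an omnibus one.** With two arms and three times the interaction has (2 − 1)(3 − 1) = 2 df. It asks whether the two profiles differ in any way, not whether the arms differ after treatment. The comparisons of clinical interest come only after it is significant.
- **The method needs complete rows.** Classical repeated-measures ANOVA in SPSS uses participants with all three visits. Someone who finishes treatment and attends T1 but misses T2 is lost to the T1 comparison too, in a trial that plans for dropouts.

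At stake is the chance of detecting the effect the trial was sized for, although the data for a sharper analysis are already being collected.

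**Working it through.** **Inputs from the protocol article.** d = 0.7012, two-sided alpha 0.05, 80% power, 70 rising to 84 participants (section 2.4); 1:1 allocation, so 42 per arm (section 2.3); three time levels including baseline (section 2.12).

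**Assumed, because the document gives none of them.** Correlation ρ between visits of 0.3, 0.5 or 0.7, equal for every pair of visits; dropout of 1/6 at random, half before T1 and half between T1 and T2; the time course of the effect.

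**Step 1: the protocol's own figure.** A two-sample t test at d = 0.7012 needs 33 per arm, or 66. The Wilcoxon–Mann–Whitney version (relative efficiency 3/π) needs 35 per arm, or 70, which matches. Then 70 × 1.2 = 84. So 70 is the size for a single two-group comparison, not for a 2-df interaction.

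**Step 2: formulas.** With n per arm and SD 1:

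- Interaction: noncentral F with 2 and 2(2n − 2) df and λ = (n/2) · Σ(δₜ − mean δ)² / (1 − ρ), where δₜ is the arm difference at visit t.
  - Sustained effect, δ = (0, d, d): the sum is 2d²/3, so λ = n d² / [3(1 − ρ)].
  - Effect halved at T2, or halved at T1 and full at T2: the sum is d²/2, so λ = n d² / [4(1 − ρ)].
- Baseline-adjusted T1 contrast: noncentral t with 2n − 3 df and noncentrality δ₁ · √(n/2) / √(1 − ρ²). This stands in for the T1 contrast of the mixed model proposed below.

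**Step 3: sample in each analysis.** Complete rows: 84 × 5/6 = 70, or 35 per arm. Present at T1: 84 × 11/12 = 77, or about 38 per arm.

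**Step 4: one case in full (sustained effect, ρ = 0.5).** d² = 0.4917.

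- Interaction: λ = 35 × 0.4917 / (3 × 0.5) = 11.47; power 86%.
- T1 contrast: 0.7012 × √19 / √0.75 = 3.53; power 94%.

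**Step 5: all cases, d = 0.7012.**

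| Setting | Test | ρ = 0.3 | ρ = 0.5 | ρ = 0.7 |
|---|---|---|---|---|
| Sustained, 1/6 dropout | Interaction (35 per arm) | 72% | 86% | 98% |
| | T1 contrast (38 per arm) | 89% | 94% | 99% |
| Halved at T2, 1/6 dropout | Interaction (35 per arm) | 58% | 74% | 93% |
| | T1 contrast (38 per arm) | 89% | 94% | 99% |
| Half at T1, full at T2, 1/6 dropout | Interaction (35 per arm) | 58% | 74% | 93% |
| | T1 contrast (38 per arm) | 35% | 41% | 56% |
| Sustained, no dropout | Interaction (42 per arm) | 80% | 92% | 99% |
| | T1 contrast (42 per arm) | 91% | 96% | 99% |

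Simulation of the sustained case with 1/6 dropout gives 71/86/98% against 89/93/99%, within a point of the formulas. Under no effect both tests reject about 5% of the time.

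**Step 6: where the gain comes from.** On the same 35 per arm, the T1 contrast has 86/92/98% against 72/86/98% for the interaction. Keeping the extra T1 attenders lifts it to 89/94/99%. Most of the gain at ρ = 0.3 and 0.5 comes from the form of the test; complete-row loss adds one to three points.

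**Step 7: if correlation decays with time.** With 10% lost by T1 and 20% by T2, a sustained effect and correlation ρ² between T0 and T2, simulated power is 64/75/91% for the interaction and 88/94/99% for the T1 contrast.

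**The case against.** The strongest reply is that repeated-measures ANOVA is a conventional, valid analysis and that its 2-df test protects against not knowing the time course. That stands. If the effect at T1 is half that at T2 and T1 is primary, at ρ = 0.5 the single contrast has 41% power and the interaction 74%. A later effect is conceivable: section 2.7.2 says the ISI, a primary measure, covers the previous month, so at T1, after a two-week course, it still includes nights before treatment. It is also true that at ρ = 0.5 or above, with a sustained effect, the planned test exceeds 80% power even after 1/6 dropout.

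A reader might infer four stronger things that the document does not support.

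- *Power is lost on every outcome.* Section 2.12 confines the ANOVA to normally distributed variables.
- *There will be no effect estimate at T1 or T2.* Post hoc comparisons are planned and can supply estimates. Reporting of differences and intervals is commonly left to a full protocol or analysis plan, which is not shown.
- *The result will be biased by restriction to completers.* The article states no deletion rule. Complete-row analysis follows from the named method in its classical form, and imputation beforehand is possible. Even without it, bias arises only if dropout is related to arm or response.
- *The diluted group main effect is the efficacy test.* The factors are written as group by time, so the interaction is the natural reading.

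**Conclusion.** The point holds as one of efficiency, not validity. Under a sustained effect at the protocol's own d, the planned interaction gives up about 18 points of power at ρ = 0.3 (71% against 89%), about 7 at ρ = 0.5 (86% against 93%) and about 1 at ρ = 0.7. At ρ = 0.3 it falls below the 80% target of section 2.4. The loss grows to about 31, 20 and 6 points if the effect halves by T2. With complete data and ρ = 0.7 it vanishes. If the effect is much smaller at the named visit, the advantage passes to the ANOVA.

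These sizes rest on assumed correlation, dropout timing and effect pattern, so no single figure should be quoted as the loss. The structure does not depend on them: baseline as a response level, a 2-df test and gated visit comparisons are all written in section 2.12. The change is worth making because section 2.5 already supplies every value it needs.

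**What to change.** For normally distributed outcomes, replace the repeated-measures ANOVA in section 2.12 with a linear mixed model (SPSS MIXED):

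- T1 and T2 values as outcomes, with the T0 value as covariate;
- arm, visit and arm × visit as fixed effects, with unstructured covariance across the two visits;
- all randomised participants with any post-baseline value, analysed in the arm to which they were randomised.

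Name the real-minus-sham difference at T1 as the primary contrast, since section 2.5 already gives T1 the role of comparing immediate efficacy. Report the T2 difference as secondary. Give both with 95% CI, whatever the other shows.

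The cost is revised wording and a different SPSS procedure, with no new data or participants; the change should be made before unblinding. There are two downsides to state. A single-visit primary contrast gives up the omnibus test's protection against an effect that appears mainly at the other visit, which deserves thought for the ISI given its one-month recall. The model also assumes data missing at random, and it still omits anyone with no post-baseline value.
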